### Exclusion criteria for all participants

Subjects will be excluded if they are seeking compensation for their injury or if they have any of the following: bilateral upper limb pain, neurological disorders, generalized musculoskeletal disorders e.g. rheumatoid arthritis or fibromyalgia, a history of low back pain and/or low back related leg pain over the previous 6 months, a history of migraine over the previous 6 months, previous surgery or trauma to the upper quadrant, diabetes or endocrine disorders, epilepsy or any psychiatric disorders. Participants taking anti-epileptic or anti-depressant medication, or who are undergoing chemotherapy/radiotherapy will also be excluded.

### Group Selection

#### Screening and Allocation to study groups

Participants will be interviewed and screened for general inclusion and exclusion criteria (Figure 1: Study Protocol). Participants with cervical radiculopathy will be recruited from a local spinal surgery service and identified by the presence of radicular pain in the upper limb, positive upper limb neurodynamic tests, Spurling's test, and Valsalva manoeuver as well as MRI confirmation of nerve compression [42,43]. The MRI scans of all patients will be reviewed by a radiologist and those patients with evidence of intervertebral disc protrusion and associated nerve root compression will be identified. Nerve root compression will be classified as absent, minimal, moderate or severe [44].

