##### • Deep tendon reflexes

Deep tendon reflexes will be assessed for Biceps (C5/6), Brachioradialis (C5/6), Pronator Teres (C**6**/7) and Triceps (C**7**/8) [45,46]. As any grade of reflex can be considered normal, reflexes will be rated normal or abnormal by comparison to the other side as it is considered that asymmetry is the most helpful assessment [47]. If reflexes are found to be abnormal, they will be further categorised as absent/diminished or increased [48]. Interrater reliability using this grading system has been found to be good for the biceps reflex [48].

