#### • Thermal Testing

All tests will be performed using a NeuroSensory Analyser (TSA 2001 II Medoc, Israel). The Peltier thermode (16 × 16 mm) will be attached directly over areas in the hand innervated by C6 (dorsum of the first metacarpal), C7 (dorsum of the second metacarpal) and C8 (dorsum of the fifth metacarpal). Tibialis anterior will be used as a reference point [35]. The temperature of the NeuroSensory Analyser will be preset to a baseline of 30 degrees Celsius and increased or decreased at a rate of 1 degree per second. Thermal detection (Warm, Cold) and pain (Heat, Cold) thresholds will be measured using the method of limits [35]. Standardised instructions will be read out to the participants prior to testing. In the case of warm and cold detection thresholds participants will be asked to indicate when they notice the temperature of the thermode changing from neutral to warm/cool and in the case of heat and cold pain thresholds participants will be asked to indicate when they notice the heat or cold becoming painful. Participants will be asked to press a patient control switch at each point. Participants will be advised that this is not a measure of pain tolerance. All measures will be taken in triplicate with the mean values used for analysis [66]. Thermal QST measures have been shown to demonstrate reasonable test-retest reliability [41,66,67].

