#### • Vibration thresholds

A Vibrameter (VSA 3000 II 2001 Medoc, Israel) will be used to measure vibration perception thresholds. Readings will be taken over the areas of the hand innervated homonymously by C6 (palmar aspect of the first metacarpal), C7 (palmar aspect of the second metacarpal) and C8 dermatomes (dorsum of the fifth metacarpal). Triplicate recordings will be taken at each site and the mean values used for analysis [35]. Test - retest reliability and [68-72] inter - rater reliability [69] has been shown to be consistently good for vibration measurements.

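### Group 2 entry names no compressed root level, but upper limb thermal and vibration thresholds are taken only at C6, C7 and C8 sites, so a patient with compression only at another root has no such reading from the affected root

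*Protocol article*

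**What the plan says.** **Entry.** Under Screening and Allocation to study groups, radiculopathy patients are "identified by the presence of radicular pain in the upper limb, positive upper limb neurodynamic tests, Spurling's test, and Valsalva manoeuver", together with MRI confirmation. A radiologist reviews the scans, and "those patients with evidence of intervertebral disc protrusion and associated nerve root compression will be identified". The grading covers severity: "Nerve root compression will be classified as absent, minimal, moderate or severe". Neither that section nor the inclusion and exclusion criteria name a root level.

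**Measurement.** Under Thermal Testing, the thermode is placed over areas of the hand "innervated by C6 (dorsum of the first metacarpal), C7 (dorsum of the second metacarpal) and C8 (dorsum of the fifth metacarpal"). The only other thermal site is on the leg: "Tibialis anterior will be used as a reference point". Under Vibration thresholds, readings are taken over "areas of the hand innervated homonymously by C6", and likewise C7 and C8.

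**Use.** The Abstract and the Background make the radiculopathy group the neuropathic comparator for NSAP. The hypothesis is that part of the NSAP group will resemble it. The sample size section rests on vibration threshold data. The Statistical Analysis section plans a one way ANOVA across groups and does not mention root level.

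**The concern.** Who enters Group 2 and where Group 2 is measured do not match. For a patient with compression at C6, C7 or C8, an analysis rule could pick out the site that belongs to the affected root. For a patient with compression only at another root, no such site exists, so no later rule can supply the reading.

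At stake is the yardstick. If thresholds in unaffected dermatomes are close to normal, including them moves the Group 2 mean towards the controls. NSAP patients with near-normal hand thresholds would then look more like radiculopathy than they should, which favours the study hypothesis for the wrong reason. Vibration, one of the two measures concerned, is also the one behind the sample size.

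**Working it through.** **1. Entry and sites side by side**

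| Compressed root | Excluded by a stated criterion? | Thermal or vibration site for that root? |
|---|---|---|
| C6, C7 or C8 | no | yes |
| Another root only (mainly C5) | no | none |

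Tibialis anterior is a remote reference and fills no gap in the upper limb. The required arm pain and positive provocation tests make high cervical roots unlikely, so C5 is the main practical case.

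**2. The plan's own figure**

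Inputs from the sample size section: effect 0.5, power 0.8, two-tailed 0.05, 50 per group.

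n per group = 2(z₀.₉₇₅ + z₀.₈₀)²/d² = 2(1.960 + 0.842)²/0.25 = 62.8, so 63 (64 with the t-test).

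Fifty per group gives 70.5% power by the normal approximation, or 69.7% by the t-test. The stated 0.8 is reached with 50 only in a one-sided calculation. That is a separate matter. Here it means only that the pairwise baseline is about 70%.

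**3. Dilution under stated assumptions**

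Let q be the share of Group 2 with no compressed root among C6 to C8. The documents do not give q, so 5% to 20% is assumed. Assume also no effect at unaffected sites, and that the site of the affected root is analysed where there is one. Then the expected effect is d = 0.5(1 − q), with the SD held at 1.

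| q | d | Power, 50 per group, two-sided t-test |
|---|---|---|
| 0 | 0.500 | 69.7% |
| 5% | 0.475 | 65.2% |
| 10% | 0.450 | 60.6% |
| 20% | 0.400 | 50.8% |

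The normal approximation gives 70.5%, 66.1%, 61.4% and 51.6%. Allowing for the extra variance from mixing changes little: at q = 20%, 51.6% becomes 50.8%.

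**4. How far these figures carry**

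The article states no root-matched analysis. Suppose each site is compared in all patients, the effect sits only in the affected dermatome, and patients divide equally over three roots (an illustration). Each site then carries 0.5/3 = 0.17 SD, with power of about 13%. A 10% share outside C6 to C8 takes this to 0.15 SD, about 12%. In that setting the extra dilution is minor, and an eligibility rule alone does not bring back 70%.

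**The case against.** Several points on the other side stand.

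- **A reader might infer that C5 patients are foreseen**, because the reflex list includes "Biceps (C5/6), Brachioradialis (C5/6"). The documents do not support this. The neurological examination is done on all subjects, controls included, and both reflexes also cover C6, a sampled root.
- **A reader might infer that the whole somatosensory profile misses the affected root.** It does not. Pressure pain thresholds are taken over three nerve trunks on both sides, the bedside sensory examination covers all upper limb dermatomes, and neurodynamic tests and questionnaires do not depend on the hand sites. The gap concerns two modalities.
- **A reader might take a fall in power from 70% to between 51% and 65% as established.** It rests on an undocumented share, on no effect at unaffected sites and on a root-matched analysis that is not stated. The Background, under QST findings in musculoskeletal disorders, reports changes on both symptomatic and asymptomatic sides in many pain conditions, so no effect away from the lesion cannot be presumed. The 0.5 is a generic medium effect based on vibration data, not a documented effect at an affected root.
- **Admitting radiculopathy without a level restriction is a legitimate choice for a descriptive comparison**, and matching sites to roots commonly belongs in an analysis plan. Figure 1 and the additional file are not visible, although nothing in the visible text points to a level rule there.

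These points limit the size of the problem. They do not remove the mismatch, because an analysis plan cannot create a reading that was never taken. It could drop such patients, but by then they would have used places among the 50.

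**Conclusion.** The point holds as a mismatch between eligibility and measurement, limited to the thermal and vibration thresholds. On the visible text, a patient with compression only at a root outside C6 to C8 can enter the neuropathic reference with no such threshold from the affected root, and this can pull the reference towards the controls.

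The size is not known. A reduction from 0.5 SD to between 0.475 and 0.40 SD follows only if the share is 5% to 20%, unaffected sites show no effect and the affected-root site is analysed. It is smaller if few such patients present or if sensory change is widespread. This is an inexpensive improvement to the reference group. It does not show that the comparison fails.

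**What to change.** Under Screening and Allocation to study groups, have the radiologist's review record the compressed root level as well as the severity grade. Require for Group 2 that at least one compressed root be C6, C7 or C8, so that the 50 places go to patients with a tested affected site. If others are enrolled, leave them out of the Group 2 thermal and vibration comparisons and do not count them towards the 50. If they were counted and then left out, 5% to 20% of 50 would leave about 47 to 40 patients, with power at 0.5 SD of about 68% to 64%.

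The cost is one line of text, one extra item recorded at a scan review that is already planned, and a small share of candidates. The reference group would then represent C6 to C8 radiculopathy only. The rule does not by itself restore the stated power. Sites would also need to be matched to the affected root in the analysis.

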**Figure 1 F1:**
[figure not shown]
**Study Protocol**.

All other participants will be screened by means of a subjective examination, pain area mapping and a clinical orthopaedic examination to identify participants with NSAP and to exclude patients with all other specific upper limb disorders according to classification criteria outlined by Boocock et al, [2]. The classification criteria for NSAP are listed in Table 1, with classification criteria for specific upper limb disorders listed in Additional file 1.

**Table 1 T1:** Classification criteria for NSAP

*DEFINITION NSAP*	*SYMPTOMS*	*SIGNS*
Pain in the arm in the absence of a specific diagnosis or pathology	Pain in the forearm and failure to meet the diagnostic criteria of specific disorders *Symptoms may include:* Loss of function Weakness in arms and hands Cramp Muscle tenderness Allodynia Slowing of fine movements Clumsiness	Absence of signs of a specific pathology that correlates with area of pain.

Boocock et al., 2009

### Data Collection

General information regarding subject health, work status, and medication use will be obtained. Information regarding the work practices of each individual will also be collected, including how many hours they spend using desktop, laptop and mouse equipment.

### Physical Examination Part B

All measures will be performed by the principal investigator. Whilst independent screening and allocation to groups would be preferable, this is not feasible within the current study and possible resultant bias is acknowledged by the authors.

#### Neurological examination

A bedside neurological evaluation of the upper limb will be carried out on all subjects, including assessment of upper limb reflexes, myotomes and sensation.

##### • Deep tendon reflexes

Deep tendon reflexes will be assessed for Biceps (C5/6), Brachioradialis (C5/6), Pronator Teres (C**6**/7) and Triceps (C**7**/8) [45,46]. As any grade of reflex can be considered normal, reflexes will be rated normal or abnormal by comparison to the other side as it is considered that asymmetry is the most helpful assessment [47]. If reflexes are found to be abnormal, they will be further categorised as absent/diminished or increased [48]. Interrater reliability using this grading system has been found to be good for the biceps reflex [48].

##### • Myotomes

Myotomes will be assessed by testing the strength of muscles corresponding to each nerve root according to previously published guidelines [49-52]. Interrater reliability for manual muscle tests ranges from κ = 0.53- 0.83 when measuring muscle strength as normal or reduced [48]

##### • Dermatomes

Sensation will be assessed for detection of light touch (using cotton wool) and sharp-blunt discrimination (using a pin prick). Stimuli will be applied circumferentially repeatedly around the participant's upper limbs so that all dermatomes will be assessed, with both limbs assessed for comparison. Each finger will be assessed separately [48]. When a difference is detected the area will be assessed in more detail and a map of the area of altered sensation will be recorded on a body chart to determine if the area follows a dermatomal pattern, is consistent with a particular peripheral nerve or if it corresponds to somatic referred pain or trigger point referral patterns [53,54]. Each sensory level will be graded as reduced, normal or increased [48]. Interrater reliability for assessment of dermatomes has been found to be moderate [48,50]. In addition, areas of heightened sensation will be assessed for signs of allodynia or hyperalgesia [15].

#### Neural Tissue Provocation Tests

Mechanosensitivity of upper limb neural tissue will be assessed using upper limb neurodynamic tests and nerve palpation.

##### • Neurodynamic Test

Longitudinal tests of the brachial plexus and peripheral nerves of the upper limb called the upper limb neurodynamic tests (ULNT) have been shown to reliably detect neural tissue mechanosensitivity [55]. The ULNT^1 ^has received the most research investigation and will be used in this study [16,35,56-60]. Interrater reliability of the ULNT^1 ^has been shown to be moderate (κ = 0.54) [43] and good (κ = 0.73) [48].

With the participant supine the test will be performed in the following sequence: gentle scapular depression, shoulder abduction, forearm supination combined with wrist and finger extension, shoulder external rotation and elbow extension [37]. Participants will be asked to indicate to the examiner during elbow extension when they first perceive pain anywhere along the tested arm. The angle of elbow extension will then be measured using a standard goniometer aligned along the mid-humeral shaft, medial epicondyle and ulnar styloid [61] and the participant will be asked to indicate their pain experienced during the test using the numerical rating scale [37].

##### • Nerve Palpation

The median, radial and ulnar nerves will be digitally palpated to assess for mechanosensitivity [62]. Nerve palpation has been used in previous studies and has shown to be reproducible [50] and moderately reliable [48]. Moderate digital pressure will be applied to each nerve at the following sites: the median nerve in the cubital fossa medial to and immediately adjacent to the biceps tendon; the ulnar nerve in the groove between the median epicondyle and the olecranon, the radial nerve in the upper arm where it passes through the intermuscular septum between the medial and lateral heads of triceps [63-65]. A test will be deemed positive if pain or symptoms are elicited [48].

### Quantitative Sensory Testing

A familiarisation trial will be performed on the brachioradialis muscle for all measures of QST prior to testing [35]. The sequence of examination will be randomised using a random number generator in order to control for the effects of fatigue.

#### • Thermal Testing

All tests will be performed using a NeuroSensory Analyser (TSA 2001 II Medoc, Israel). The Peltier thermode (16 × 16 mm) will be attached directly over areas in the hand innervated by C6 (dorsum of the first metacarpal), C7 (dorsum of the second metacarpal) and C8 (dorsum of the fifth metacarpal). Tibialis anterior will be used as a reference point [35]. The temperature of the NeuroSensory Analyser will be preset to a baseline of 30 degrees Celsius and increased or decreased at a rate of 1 degree per second. Thermal detection (Warm, Cold) and pain (Heat, Cold) thresholds will be measured using the method of limits [35]. Standardised instructions will be read out to the participants prior to testing. In the case of warm and cold detection thresholds participants will be asked to indicate when they notice the temperature of the thermode changing from neutral to warm/cool and in the case of heat and cold pain thresholds participants will be asked to indicate when they notice the heat or cold becoming painful. Participants will be asked to press a patient control switch at each point. Participants will be advised that this is not a measure of pain tolerance. All measures will be taken in triplicate with the mean values used for analysis [66]. Thermal QST measures have been shown to demonstrate reasonable test-retest reliability [41,66,67].

#### • Vibration thresholds

A Vibrameter (VSA 3000 II 2001 Medoc, Israel) will be used to measure vibration perception thresholds. Readings will be taken over the areas of the hand innervated homonymously by C6 (palmar aspect of the first metacarpal), C7 (palmar aspect of the second metacarpal) and C8 dermatomes (dorsum of the fifth metacarpal). Triplicate recordings will be taken at each site and the mean values used for analysis [35]. Test - retest reliability and [68-72] inter - rater reliability [69] has been shown to be consistently good for vibration measurements.

#### • Pressure Pain Thresholds

Pressure pain thresholds (PPT) will be determined using a hand held pressure algometer with a probe size of 1 cm2 (Somedic AB, Farsta, Sweden) and an application rate of 40 kPa/s. PPT will then be recorded bilaterally over the median, ulnar and radial nerves, the sites of which will correspond to the nerve palpation sites outlined above [65]. All sites will be marked with a skin marker to ensure accuracy [73]. The participant will be instructed to press a patient control switch when the sensation under the probe changes from one of pressure to one of pressure and pain. All measures will be taken in triplicate and the mean value was used for analysis [35]. PPT measures have been repeatedly shown to demonstrate good intra and inter - rater reliability both in general [74-78] and in sites specific to the upper limb nerves [65]

### Pain Assessment

Participants from both patient groups will be asked to complete a detailed assessment of pain intensity and quality. A clinically administered LANSS questionnaire will be used for specific identification of neuropathic pain. The LANSS has been tested and validated in several settings [79-81]. A Short Form McGill Pain Questionnaire will be administered [82], which has been validated for the measurement of sensory and affective dimensions of pain [83]. The McGill includes a visual analogue scale and present pain index [82,84]. A Tampa Scale for Kinesiophobia will be used as this has been shown to be a reliable assessment tool for chronic pain [85-87,82-84] while the DASH [88,89] and SF-36 will be used as measures of disability and functional impairment in these patient groups. Furthermore, three proposed algorithms, which are currently under review by other researchers, will be used as aids in differentiation of pain mechanisms for all symptomatic subjects [12-14].

### Data Management

Participant data will be coded to ensure anonymity of participants and stored at a central database at the School of Physiotherapy and Performance Science, University College Dublin, Ireland.

### Sample size/power calculation

Power analysis: Sample size was calculated based on mean and standard error vibration threshold data from a study by Greening et al., (2003). A sample of size of 50 patients with NSAP, 50 patients with cervical radiculopathy and 50 matched control subjects will be required to detect a medium effect size (0.5) with 0.8 power and 0.05 two tailed significance level.

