### Participants

One hundred and fifty consenting male and female subjects, aged 18-65 years will be recruited comprising three equal groups of (1) Patients with NSAP, (2) Patients with cervical radiculopathy and (3) Age and gender matched controls.

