### Statistical Analysis

Descriptive statistics will be calculated for all outcome measures. Differences in categorical variables between groups will be analysed using a Chi Square Test. A one way ANOVA with Student-Newman-Keuls test will be used for Post-hoc comparisons for all continuous normally distributed data.

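### Fifty per group gives about 70% power, not the stated 80%, for a two-tailed comparison at a standardised difference of 0.5

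*Protocol article*

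**What the plan says.** Under *Sample size/power calculation* the protocol article states that 50 subjects in each of the three groups "will be required to detect a medium effect size (0.5) with 0.8 power and 0.05 two tailed significance level". The scale of the effect size is not named. Under *Participants*, 150 subjects "will be recruited comprising three equal groups of (1) Patients with NSAP, (2) Patients with cervical radiculopathy and (3) Age and gender matched controls", which agrees with 50 per group.

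Under *Statistical Analysis* the method for continuous outcomes is: "A one way ANOVA with Student-Newman-Keuls test will be used for Post-hoc comparisons for all continuous normally distributed data". The sample size section mentions no pairing, multiplicity adjustment or one-sided test.

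**The concern.** A two-group comparison at a standardised difference of 0.5, two-sided 5% level and 80% power is a standard case, and its answer is 63 or 64 per group. Fifty is visibly too few.

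The sentence is the article's only justification for the sample size. It promises a type II error of 20% at the stated effect, whereas a single two-tailed comparison has about 30%. The objectives include comparing NSAP with cervical radiculopathy and with controls. A reader weighing a non-significant difference between two groups would rely on this figure and would trust the null result more than the design warrants.

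**Working it through.** **Inputs, all from the protocol article.** n = 50 per group in three equal groups; effect size 0.5, taken as d, a difference in SD units; power 0.80; alpha 0.05 two-tailed. The analysis is an unpaired one-way ANOVA followed by Student-Newman-Keuls (SNK).

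**1. Attempt to reproduce n = 50, normal approximation.** n per group = 2(z_alpha + z_beta)² / d².
- Two-tailed: 2(1.960 + 0.842)² / 0.25 = 62.8, so 63.
- One-tailed: 2(1.645 + 0.842)² / 0.25 = 49.5, so 50.

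**2. The same with the t distribution.** The noncentral t has 2n − 2 degrees of freedom and noncentrality d√(n/2).
- Two-tailed: 63.8, so 64 per group. That is 3 × 64 = 192 in total, and 64/50 = 1.28 times the stated size.
- One-tailed: 50.2, so strictly 51.

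The stated n is therefore not reproduced under the stated two-tailed level.

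**3. Power at n = 50 per group, d = 0.5.** Noncentrality = 0.5 × √25 = 2.5.
- Two-tailed, normal: Φ(2.5 − 1.960) = Φ(0.540) = 0.705. By t: 0.697.
- One-tailed, normal: Φ(2.5 − 1.645) = Φ(0.855) = 0.804. By t: 0.799.

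**4. Difference detectable with 80% power at n = 50, two-tailed t.** Power is 0.777 at d = 0.55 and 0.800 at d = 0.566, so about 0.57 SD.

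**5. Overall F test, N = 150.** Noncentrality is f²N, with 2 and 147 degrees of freedom.

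| Reading | f | f²N | Power | n per group for 80% |
|---|---|---|---|---|
| *Medium* on the ANOVA scale | 0.25 | 9.375 | 0.780 | 53 |
| 0.5 taken as f | 0.5 | 37.5 | >0.999 | 14 |
| Means 0, 0, 0.5 | 0.236 | 8.33 | 0.727 | 59 |
| Means 0, 0.25, 0.5 | 0.204 | 6.25 | 0.593 | 79 |

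None of these returns 50 per group with power 0.80.

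**6. ANOVA then SNK, power for a pair 0.5 SD apart.** This was simulated with 200,000 replicates and 50 per group. The third mean is an assumption, because the article gives none.

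| Third group's mean | SNK after a significant F | SNK alone |
|---|---|---|
| Equal to one of the pair | 0.62 | 0.62 |
| Midway between the pair | 0.56 | 0.57 |
| 0.5 SD beyond the pair | 0.70 | 0.70 |

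The upper figure is a ceiling. SNK never declares a pair different unless the pair exceeds the two-mean critical value, which is the ordinary t criterion with pooled variance on 147 degrees of freedom. The power of that test at this difference is 0.700.

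**7. Other routes to 80%.**
- A paired analysis of matched subjects would have power 0.78 at a within-pair correlation of 0.2 and 0.81 at 0.25.
- Comparing one group with the other two pooled (50 against 100) would have 0.82.

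Neither analysis is in the plan.

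**The case against.** The best defence is that the article does not name the effect-size scale. For a three-group ANOVA *medium* is conventionally f = 0.25, which corresponds to d = 0.5 when there are only two groups. On that reading the shortfall is 0.78 against 0.80, a near miss. This should be disclosed. It does not clear the sentence, because the printed figure is 0.5 and 0.78 is still below 0.80.

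A reader might infer several stronger points that the article does not support:

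- *That power under ANOVA with SNK is about 61%, and always lower than for a single comparison.* A figure near that arises only if the third mean equals one of the other two. If the third mean lies beyond the pair, SNK costs essentially nothing. Only a range can be given.
- *That a one-tailed calculation was mislabelled.* The normal approximation does give 50, but the exact t calculation gives 51. This is a plausible cause and no more.
- *That citing source data and then quoting 0.5 is itself an error.* The article says "Sample size was calculated based on mean and standard error vibration threshold data" from an earlier study. A standardised effect can be derived from such data and then described as medium. The source figures are not shown, so no mismatch can be demonstrated, and an article may leave that detail to the full protocol.
- *That the study will misreport null results as similarity.* The Background hypothesises that some NSAP patients may resemble those with radiculopathy, but no equivalence claim is planned.

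**Conclusion.** The power statement is wrong as written. With 0.5 as a standardised mean difference and a two-tailed 5% level, 50 per group gives about 70% power for one pairwise comparison, ten points below the claim; 64 per group would be needed. Under the planned ANOVA with SNK, power for such a pair is about 56-70%, so no third-group pattern examined reaches 80%.

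The 70% figure rests on reading 0.5 as d, on normally distributed data with equal variances, and on unpaired groups of exactly 50. The 56-70% range rests also on assumed positions of the third mean. The most favourable reading of *medium*, f = 0.25, reduces the gap to two points but does not close it. The finding concerns the stated power; it does not show that 150 participants are unusable.

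**What to change.** Keep 150 participants and replace the claim of 80% power at 0.5 with a sentence such as:

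> Fifty per group gives about 70% power for a single two-tailed comparison at a standardised difference of 0.5 (about 56-70% under ANOVA with Student-Newman-Keuls, depending on the third group's mean); 80% power is reached for a difference of about 0.57 SD in a single unadjusted comparison.

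This changes one sentence, with no extra participants and no change to the analysis. The cost is that the stated power becomes less favourable.
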